**Methods/design:**

This is a single-center, randomized, placebo-controlled clinical phase 2 trial, investigating the clinical superiority of Salovum® given as a food supplement during 5 days to adults with severe TBI (Glasgow Coma Scale (GCS) < 9), admitted to the neurocritical intensive care unit (NICU) at Skane university hospital, Lund, Sweden. All patients with GCS < 9 and clinical indication for insertion of ICP-monitor and microdialysis catheter will be screened for inclusion and assigned to either the treatment group (*n* = 10) or placebo group (*n* = 10). In both groups, the primary outcome will be ICP (mean values and change from baseline during intervention), registered from high-frequency data monitoring for 5 days. Secondary outcomes will be inflammatory mediators in plasma and intracerebral microdialysis perfusate days 1, 3, and 5 during trial treatment.

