## Methods/design

### Trial design

This is a single-center, investigator-sponsored, phase 2, randomized, placebo-controlled, parallel-arm trial to assess the superiority of AF given as Salovum® in patients with severe TBI. The allocation ratio is 1:1. Recruitment commenced in March 2020.

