### Trial population and eligibility

A total of 20 patients with severe TBI will be enrolled at a single study site, Skane University Hospital, Lund Sweden. Patients with a Glasgow Coma Scale (GCS) score < 9 and clinical indication for insertion of ICP monitor, intracerebral oxygen pressure monitor (Licox®), and microdialysis catheter will be screened for inclusion.

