#### Study endpoints

The primary endpoint is the effect of AF, given as a dietary supplement in the form of Salovum®, compared with placebo on ICP [24]. The secondary endpoint is the effect on inflammatory mediators [25] in patients with severe TBI. Exploratory endpoints include intracerebral oxygen pressure (PbtO_2_) [26], cerebral perfusion pressure (CPP), mortality at 30 days, therapy intensity level (TIL, see page 9) [27, 28], brain metabolites [29, 30], ICP change from baseline, ICP under the curve and outcome according to the extended Glasgow Outcome Scale (eGOS) at 6 months. Binary outcome variables (i.e., 30-day mortality) will be analyzed using the chi-square test. For continuous data, the Mann–Whitney *U* test will be used. All computations will be run with the free statistical software R (https://www.r-project.org).

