#### Data collection of outcome parameters and predefined covariates

Basic parameters (GCS, GCS-T, age, gender, medical history, diagnosis) are collected from electronic medical charts (Melior) and the monitoring system (IntelliSpace Critical Care and Anesthesia [ICCA] system; Philips) at the NICU. High-frequency data collection of physiological parameters (ICP, CPP, PbtO_2_, pulse, blood pressure, PO_2_, temperature) are sampled with a Moberg® CNS monitor. Brain metabolites (Lactate/pyruvate ratio, glucose, glutamate, glycerol) are analyzed using ISCUS flex (M Dialysis AB). All data from the Moberg CNS monitor and other electronic sources will be transferred to an electronic CRF (Redcap). TIL will be scored every 24 h. TIL will be recorded in a paper CRF and then transferred to the electronic CRF continuously., Plasma samples will be collected before the initial dose of the trial substance, thereafter twice daily for 5 days, and after the last dose of the trial substance. After centrifugation, aliquoted samples will be stored in a − 80 °C freezer. The plasma will be analyzed for markers of brain damage and cytokines/chemokines. Similarly, microdialysis perfusate fluid will be stored in a − 80 °C freezer and analyzed for cytokines/chemokines and markers for brain damage (see Tables 1 and 2). Age, gender, GCS, GCS-T, and trauma mechanism at inclusion, may be used as covariates in exploratory regression analysis. Medical charts are used to track 30-day mortality. Patients or next of kin are followed up by visits and/or telephone interviews at the outpatient clinic in order to assess eGOS > 6 months. All data is stored in a specific password-protected eCRF, only accessible to investigators (Fig. 1).

**Table 1 Tab1:** Primary and secondary outcome measures

Outcome measure	Measure description	Time frame	Objective
ICP mean	Measured by an intracranial pressure sensor	During intervention, 5 days	Primary
ICP area under curve	Measured by an intracranial pressure sensor	During intervention, 5 days	Primary
Inflammatory cytokine secretion	Interleukin-6 (Il-6), interleukin-8 (IL-8), Interferon-gamma inducible protein (IP10) and monocyte chemotactic protein (MCP-1) assessed from microdialysate and plasma by multiplex analysis	During intervention, 5 days	Secondary

**Table 2 Tab2:** Exploratory outcome measures

Outcome measure	Measure description	Time frame
Mortality	Mortality due to TBI	At 30 days and 12 months

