#### Statistical power of proposed endpoints

This is an exploratory trial with no previous data to calculate power.

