#### Statistical analysis

Binary outcome data (e.g., mortality) will be analyzed with the chi-square test. Continuous data will be analyzed using the Mann–Whitney *U* and Wilcoxon tests. Both per-protocol and intent-to-treat analyses will be performed. All statistical calculations will be conducted in R Studio. Please see Additional files 1 and 3 for detailed information.

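### The primary comparison of 5-day ICP is a rank test without adjustment for baseline ICP; with 10 patients per arm, adjusting would add power, substantially so if the baseline correlation is about 0.5 or more

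*Protocol article*

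**What the plan says.** All places are in the protocol article.

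- **Tests.** Study endpoints: "For continuous data, the Mann–Whitney *U* test will be used". Statistical analysis: "Continuous data will be analyzed using the Mann–Whitney *U* and Wilcoxon tests". The second sentence adds a Wilcoxon test without saying whether it is the rank-sum or the signed-rank version, or what it is applied to. The section refers to Additional files 1 and 3 for detail.
- **Primary outcome.** Table 1 marks ICP mean and ICP area under the curve as primary, each with the time frame "During intervention, 5 days". Neither refers to baseline.
- **Use of baseline.** The abstract says "the primary outcome will be ICP (mean values and change from baseline during intervention". The Study endpoints section and Table 2 instead place ICP change from baseline among the exploratory outcomes. The Study endpoints section also lists ICP under the curve as exploratory, against Table 1.
- **Covariates.** The data collection section names age, gender, GCS, GCS-T and trauma mechanism, and says that they "may be used as covariates in exploratory regression analysis". Baseline ICP is not on the list.
- **Size.** "A total of 20 patients with severe TBI will be enrolled at a single study site", and "The allocation ratio is 1:1", so 10 per arm. On power: "This is an exploratory trial with no previous data to calculate power".

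**The concern.** A two-sample rank test on the 5-day mean or area under the curve cannot use each patient's ICP before the first dose. With 10 per arm, randomisation leaves sizeable chance differences in baseline ICP, and the part of later ICP that baseline predicts stays in the comparison as noise. The plan already needs the baseline value, so adjusting for it requires no new data. The Trial population section fixes 20 patients and the enrolment section reports about 15 severe TBI cases a year at the site, so precision cannot easily be bought with more patients.

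A second, smaller matter is the unexplained Wilcoxon test. The rank-sum version is the Mann–Whitney test itself. The wording is therefore either redundant or means a paired signed-rank test, which on change-from-baseline data would compare before with after inside one arm. Such a test picks up natural course and routine ICP treatment as well as any effect of the product.

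**Working it through.** **Inputs from the article:** 10 per arm; Mann–Whitney test for continuous data; 5-day outcome without a baseline term. The article gives no power, effect size or SD, so there is no figure to reproduce.

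**Assumptions:** two-sided 0.05; correlation r of baseline ICP with 5-day ICP of 0.3, 0.5 or 0.7; true difference of 1 SD; normal data.

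**1. Chance imbalance.** The SD of the between-arm difference in mean baseline is sqrt(2/10) = 0.447 SD. It enters the unadjusted outcome difference multiplied by r: 0.447 × 0.3 = 0.13, × 0.5 = 0.22, × 0.7 = 0.31 SD.

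**2. What adjustment is worth (normal approximation).** ANCOVA reduces the residual variance by the factor 1 − r².

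- Effective n per arm, 10/(1 − r²): 10/0.91 = 11.0; 10/0.75 = 13.3; 10/0.51 = 19.6.
- Difference detectable with 80% power, unadjusted: (1.960 + 0.842) × 0.447 = 1.25 SD. Multiplied by sqrt(1 − r²), it becomes 1.195, 1.085 and 0.895 SD.

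**3. Simulated power at a 1 SD difference** (10 per arm; repeated runs agree to about 0.01, apart from 0.51–0.53 for the unadjusted Mann–Whitney test):

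| Between-arm analysis | r = 0.3 | r = 0.5 | r = 0.7 |
|---|---|---|---|
| Mann–Whitney, 5-day value | 0.51 | 0.51 | 0.51 |
| Mann–Whitney, change from baseline | 0.39 | 0.52 | 0.74 |
| Rank-ANCOVA | 0.56 | 0.62 | 0.75 |
| ANCOVA | 0.58 | 0.66 | 0.81 |

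ANCOVA therefore gains about 7, 15 and 30 points over the unadjusted rank test, and rank-ANCOVA about 5, 11 and 24. With no true difference, the rejection rate is about 0.05 for ANCOVA and rank-ANCOVA and about 0.04 for the exact Mann–Whitney test.

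**4. How much of the gain is due to baseline.** An unadjusted t-test in the same setting has power of about 0.56. Against it, ANCOVA gains about 2 points at r = 0.3, 10 at r = 0.5 and 25 at r = 0.7. At r = 0.3, most of the difference from Mann–Whitney comes from replacing an exact rank test with a parametric test on normal data.

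**5. Smaller effect.** At a 0.5 SD difference, power is 0.16 for Mann–Whitney against 0.19, 0.22 and 0.30 for ANCOVA. Neither analysis is well powered there.

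**6. If the Wilcoxon test is a within-arm signed-rank test.** Assume no treatment effect and the same drift of 0.3 to 0.8 SD in both arms, with r = 0.5 or 0.7. The chance p that a given arm is significant ranges from 0.135 to 0.811. The chance of a significant change on active but not on placebo is p(1 − p), for example 0.135 × 0.865 = 0.12 and 0.429 × 0.571 = 0.24. Over the settings tried it runs from 12% to about 25%, and 25% is its ceiling, reached at p = 0.5. The between-arm Mann–Whitney test on change rejects in 4% to 5% of the same trials.

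**The case against.** The strongest reply has five parts.

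- **Baseline is not ignored.** ICP change from baseline is a planned outcome, and primary according to the abstract. This stands: a reader might infer that the plan disregards baseline altogether, and it does not. But a change score fixes the baseline coefficient at 1. Its power is below the unadjusted test at r = 0.3, about equal at r = 0.5, and close to rank-ANCOVA only at r = 0.7.
- **The correlation is unknown and may be low.** The article describes active ICP treatment, including CSF drainage, barbiturate coma and craniectomy, which could weaken the link between baseline and the 5-day mean. This stands. A reader might infer that the plan certainly gives away much of its power; the article does not support that.
- **Part of the gain comes from changing the type of test.** This also stands, as step 4 shows. A gain due to baseline remains at r = 0.5 and above.
- **The within-arm reading of Wilcoxon is inference.** The article never says paired or within-arm, and its stated aims are between-arm. A reader might infer that before/after efficacy claims are planned, but no such claim is written. If within-arm tests were used, the harm would be false conclusions, not lost power.
- **The trial is exploratory and detail sits in additional files.** An unadjusted rank test between randomised arms is valid, so this is a loss of efficiency and not an error. The additional files may say more. Still, the article does fix the test, the primary outcome and the covariate list, and it describes the aim as superiority, so a better use of data already collected is a fair request.

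**Conclusion.** The point holds in a limited form. As the article states it, the primary between-arm comparison of 5-day ICP mean and area under the curve does not adjust for baseline ICP, although the value is needed for other outcomes and is absent from the covariate list. For an assumed 1 SD difference at 10 per arm, adjustment raises power from about 0.51 to between 0.56 and 0.81, depending on the method and on a correlation assumed to lie between 0.3 and 0.7. The benefit is minor at 0.3 and worth having from about 0.5. These figures assume normal data and two-sided 0.05; none of the inputs other than the sample size and the test comes from the article.

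Two textual matters need settling whatever the correlation: the abstract and the endpoint sections disagree on whether change from baseline is primary, and the Wilcoxon test has no stated type or purpose.

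**What to change.** 1. Before unblinding, make the primary analysis of 5-day ICP an ANCOVA on arm and pre-dose ICP, on the log or rank scale if the data are skewed. Report the adjusted between-arm difference with a 95% CI.
2. Keep the unadjusted Mann–Whitney test as a sensitivity analysis.
3. Reconcile the abstract with the Study endpoints section and Tables 1 and 2 on the status of change from baseline, and the Study endpoints section with Table 1 on the area under the curve.
4. State which Wilcoxon test is meant. If it is a within-arm signed-rank test, label it descriptive and not evidence of efficacy.

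The cost is a change of wording, one degree of freedom (17 residual instead of 18) and a linearity assumption, which the rank-based analyses help to check. No new data are needed. The article says that investigators stay blinded throughout and that no interim analysis is done, so the change can be made without knowledge of results. If unblinding has already taken place, the adjusted analysis should be reported as added afterwards.

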#### Handling of missing data

With the exception of TIL, the data collected in this trial is limited to what is normally measured and registered during standard care at the NICU. Therefore, the amount of missing data is expected to be low. Data missing at random will be handled using the last observation carried forward (LOCF). Data not missing at random will be analyzed using mean substitution. If microdialysis is not initiated or fails after insertion, the patient will be given the trial substance or placebo as scheduled, but additional patients will be added in order to achieve 20 patients monitored with microdialysis data for a minimum of 3 days.

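### LOCF for data missing at random and mean substitution for data not missing at random do not fit those mechanisms, and can bias the 5-day ICP summaries

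*Protocol article*

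**What the plan says.** The section Handling of missing data in the protocol article pairs one method with each mechanism: "Data missing at random will be handled using the last observation carried forward (LOCF). Data not missing at random will be analyzed using mean substitution". The article does not say whether that mean is the patient's own, the arm's or the pooled mean.

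The same section argues that nearly everything except TIL is routine intensive-care data, and concludes: "Therefore, the amount of missing data is expected to be low". It gives no figure. If microdialysis fails or is never started, "additional patients will be added in order to achieve 20 patients monitored with microdialysis data for a minimum of 3 days".

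The abstract says ICP is "registered from high-frequency data monitoring for 5 days", and Table 1 lists the 5-day ICP mean and ICP area under the curve as primary. Continuous outcomes are compared by Mann–Whitney U and Wilcoxon tests (Statistical analysis), in 10 patients per arm. That section refers to Additional files 1 and 3 for detail; they are not shown here.

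**The concern.** Missing at random means that missingness depends only on what was observed, so observed data can be used to predict the missing values. It does not imply that a value stays where it was last seen. LOCF needs that second, much stronger assumption. The trial itself expects ICP and the mediators to move: Table 2 lists change from baseline for both.

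Not missing at random means that missingness depends on the unseen value. The mean of those still observed is then the wrong value for those who are not, so mean substitution fails in exactly the situation it is reserved for.

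Both are single imputations, so later calculations count filled-in values as real measurements. The choice between the rules rests on a mechanism that the data cannot identify. In a comparison of 10 against 10, moving one or two patients in the ranking matters. What is at stake is the primary ICP estimate, on which the Discussion would base support for further use of the product.

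**Working it through.** **Inputs from the article.** "A total of 20 patients with severe TBI will be enrolled at a single study site"; "The allocation ratio is 1:1"; hence 10 per arm, as the abstract states. Outcome: 5-day ICP. Test: Mann–Whitney. The article gives no missing-data rate, ICP level, SD, effect size or alpha, so there is no figure of its own to reproduce.

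**Inputs assumed.** Two-sided alpha 0.05. Daily mean ICP 14, 17, 18, 16, 13 mmHg; between-patient SD 4; within-patient SD 3; lag-1 correlation 0.6; no treatment effect. Monitoring stops early under several mechanisms.

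**Step 1: how much weight LOCF can give one value.** If monitoring stops at 72 h of 120 h, the carried value fills 48/120 = 40% of the 5-day mean. Whether that value is a single reading or a daily mean is not stated. For microdialysis, requiring at least 3 of 5 days tolerates up to 2/5 = 40% of days missing per patient.

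**Step 2: days missing within patients.** There were 4,000 simulated trials per row. Each cell shows the spurious arm difference in mmHg, then the Mann–Whitney rejection rate. The Monte Carlo standard error of a 5% rate is √(0.05 × 0.95/4000) = 0.3 percentage points.

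| Mechanism (days missing, arm A / arm B) | Full data | LOCF | Pooled day mean | Arm day mean | Patient's own mean |
|---|---|---|---|---|---|
| Completely random (18% / 18%) | 0.04; 4.2% | 0.05; 4.1% | 0.04; 3.9% | 0.06; 12.7% | 0.05; 4.3% |
| Completely random (4% / 39%) | 0.01; 4.2% | 0.02; 4.1% | 0.01; 2.9% | 0.03; 14.6% | −0.22; 4.2% |
| At random, stops after low ICP (3% / 34%) | −0.05; 4.1% | −0.50; 4.3% | 0.87; 5.4% | 1.29; 17.3% | −0.56; 4.5% |
| Not at random, low ICP unseen (3% / 29%) | 0.01; 4.3% | 0.10; 4.4% | 1.00; 5.9% | 1.40; 16.2% | −0.02; 4.5% |
| Not at random, low unseen in A, high in B (14% / 15%) | −0.05; 4.3% | −0.14; 4.4% | −0.94; 5.8% | −1.20; 14.5% | −0.20; 4.5% |

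Where not-at-random missingness worked alike in both arms (14 to 15% of days), no arm difference appeared. Pooled-mean substitution still shifted the overall ICP level: 16.20 against 15.63 when low values were unseen (+0.6), and 15.00 against 15.59 when high values were unseen (−0.6).

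**Step 3: whole patients missing.** There were 20,000 simulated trials per case, with m of 10 missing in each arm.

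| m | Arm mean substituted | Pooled mean substituted |
|---|---|---|
| 1 | 7.3% | 4.7% |
| 2 | 12.8% | 4.6% |
| 3 | 19.4% | 4.4% |
| 4 | 30.6% | 4.7% |

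A separate run of 20,000 trials gave 12.6% for m = 2 and 19.9% for m = 3 with arm means.

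**Step 4: why arm means inflate.** The apparent standard error of an arm mean, divided by the correct one, is [√((9 − m)/9)/√10] ÷ [1/√(10 − m)]. For m = 2 this is (0.882/3.162) ÷ 0.354 = 0.789, or 21% too small. For m = 3 it is (0.816/3.162) ÷ 0.378 = 0.683, or 32% too small. An imputation that ignores arm leaves the arms exchangeable when missingness works alike in both, so the rank test then keeps its level.

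**The case against.** The strongest defence is that the trial is exploratory, makes no power claim and expects few gaps. ICP monitoring is a condition of entry and routine care, and patients without adequate microdialysis data are supplemented by further recruitment. The additional files may also say which mean is used, how mechanisms are classified and what sensitivity analyses are planned. Much of this stands. It limits the likely size of the problem, and the absence of those details from an article is no fault. It does not rescue the two pairings, which are stated in the article and which added detail would not make valid.

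A reader might go further in three ways that the documents do not support.

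- **That both rules inflate false positives.** They do not as written. LOCF stayed at 4.1 to 4.5% in every simulated scenario, patient-mean substitution at 4.2 to 4.5%, and pooled-mean substitution at no more than about 6%. Marked inflation needs the arm's own mean, which the text neither specifies nor excludes.
- **That the section contradicts itself** by expecting little missing data while planning extra patients. A contingency for catheter failure is compatible with that expectation.
- **That monitoring will stop mainly through death or recovery, and that hours after death would be filled in.** The article states neither. That early stopping may be linked to ICP is a reasonable inference in this population, but only an inference. Examples that impute ICP after death rest on a rule the article does not give.

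**Conclusion.** The concern holds in this limited form, as a point that should be fixed. Both rules are mismatched to the mechanisms they are assigned to, and following them can bias the ICP mean and area under the curve.

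The sizes found depend on the assumed ICP course, SDs and missing rates. The larger spurious differences arose only when missingness differed between arms, in amount or in direction. With LOCF the difference was 0.5 mmHg, at 3% against 34% of days missing. With a pooled mean it was about 0.9 to 1.0 mmHg, and with arm means up to 1.4 mmHg. With few gaps, or gaps arising alike in both arms, the effect on the comparison is small unless arm means are used. Type I error is a serious issue only under arm-mean substitution. All simulations assume no treatment effect, so they do not show how a real effect would be distorted.

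**What to change.** Delete both rules and fix the following before unblinding.

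1. **Under missing at random**, analyse all observed data with a mixed model of 24-h ICP means on arm, day and baseline ICP, with mediators on the log scale. Alternatively, keep the planned Mann–Whitney test and precede it with multiple imputation, stating the imputation model and how results are combined. Either is acceptable; choose one.
2. **For not-at-random missingness**, use sensitivity analyses instead of a single filled-in value: a worst-rank analysis for deaths within 5 days, and a delta-adjusted or tipping-point analysis.
3. **If any mean substitution is kept**, state which mean, and do not use arm-specific means.
4. **A simple mean over monitored hours** should be supportive only, because patients who stop early are then summarised over different days.

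The cost is revised wording in the protocol and analysis plan and modest extra programming, with no new patients or data. The downside is a model assumption in a sample of 20. The mixed model does not itself deal with not-at-random missingness, which is why item 2 is needed.

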### Study participants

Study participants will be composed of 20 patients with severe TBI (GCS < 9) who are planned for neurointensive care, including ICP monitoring, microdialysis, and intracerebral oxygen pressure monitoring. When a patient with severe traumatic brain injury is admitted to the neurointensive care unit, the neurosurgeon on call or study investigator will evaluate the patient, provide next of kin with informed consultation, and use the screening protocol for inclusion. For patients < 18 years, signed informed consent by next of kin is required for inclusion.

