### Randomization

Patients in the trial are allocated to treatment with Salovum® or placebo egg yolk powder at a ratio of 1:1. The allocation sequence is generated by the principal investigator. Permuted block randomization, with blocks of 4–6, will be used and was compiled with R. Each patient is assigned a sequentially numbered study binder. The study number written in the binder corresponds to a sealed and opaque box with the same number, containing the study substance, either active (Salovum®) or placebo (normal egg yolk powder). Study substance and placebo appear identical with respect to packaging, color, texture, and smell. Investigators, caregivers, and patients are blinded during the entire trial. If any patient needs unblinding for medical reasons, an emergency unblinding list exists in digital form.

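### Adding patients until 20 have 3 days of microdialysis data cannot be squared with a total enrolment of 20 (10 per arm), and the rule's trigger does not match its target

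*Protocol article*

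**What the plan says.** Three places in the protocol article give a fixed size. The abstract has patients "assigned to either the treatment group (*n* = 10) or placebo group (*n* = 10". Trial population and eligibility states: "A total of 20 patients with severe TBI will be enrolled at a single study site". Study participants repeats it: "Study participants will be composed of 20 patients with severe TBI (GCS < 9) who are planned for neurointensive care". Trial design adds that "The allocation ratio is 1:1", and Randomization that "Permuted block randomization, with blocks of 4–6, will be used".

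Handling of missing data attaches a different meaning to 20. If microdialysis is never started, or stops working once the catheter is in, the patient still receives the assigned powder, but "additional patients will be added in order to achieve 20 patients monitored with microdialysis data for a minimum of 3 days". No upper limit on the number randomised is given.

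The primary endpoint is ICP (Study endpoints; Table 1), which does not need a microdialysis catheter. Microdialysis feeds the secondary cytokine outcome and some exploratory ones. On analysis sets, Statistical analysis says: "Both per-protocol and intent-to-treat analyses will be performed". It refers to Additional files 1 and 3 for detail. Those files are not at hand.

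**The concern.** The number 20 is used for two different things: patients enrolled, and patients with at least 3 days of microdialysis data. They coincide only if every enrolled patient reaches 3 days. Otherwise the stated total and the stated 10 per arm are both wrong, and a reader of the final report cannot tell which count was the plan.

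The rule is also mismatched internally. What sets it off is a technical event, but what ends it is a duration observed after allocation and dosing. A patient who dies, or whose monitoring is withdrawn, on day 2 with a working catheter does not meet the trigger, yet does not count toward the 20 either. Read by its trigger, the rule adds nobody for such a patient; read by its target, it does. In severe TBI, with 30-day mortality among the exploratory endpoints, that case is foreseeable.

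At stake is the meaning of the sample size and, if an analysis were later confined to the 20 who reached 3 days, whether the compared groups would still be the randomised groups.

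**Working it through.** **The plan's own figure.** 10 + 10 = 20 agrees with the stated total. There is nothing further to reproduce, since the article says that no earlier data were available for a power calculation and gives no effect size, SD or alpha.

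**Inputs.** From the documents: target of 20 patients with at least 3 days of data; 1:1 allocation; permuted blocks of 4–6. Assumed: the share q of randomised patients who do not reach 3 days, for any reason. The documents give no rate (they expect little missing data), so a range of 5% to 30% is shown.

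**Number randomised.** If enrolment stops at the 20th patient with 3 days of data:
- mean number randomised = 20/(1 − q). For q = 10%: 20/0.9 = 22.2; 20%: 20/0.8 = 25.0; 30%: 20/0.7 = 28.6.
- chance that more than 20 are randomised = 1 − (1 − q)^20. For q = 5%: 1 − 0.95^20 = 0.64.

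**Split among the 20 evaluable.** Simulation of 20,000 trials per rate, each block being of size 4 or 6 with equal chance, the same loss in both arms, stopping at 20 evaluable patients:

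| q (assumed) | Mean randomised | 5th–95th percentile | More than 20 randomised | Exactly 10:10 | 12:8 or worse |
|---|---|---|---|---|---|
| 5% | 21.1 | not simulated | 64% | not simulated | not simulated |
| 10% | 22.2 | 20–25 | 88% | 48% | 6% |
| 20% | 25.0 | 21–29 | 99% | 37% | 15% |
| 30% | 28.6 | 23–35 | over 99% | 31% | 23% |

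With no losses at all, the same simulation gives 10:10 in 77% of trials, because 20 need not fall at the end of a block. That shortfall comes from the assumed block order and not from the rule: a list such as 4 + 4 + 6 + 6 = 20 would give 10:10 exactly. If loss were 30% in one arm and 10% in the other, 10:10 would occur in 19% of trials and 12:8 or worse in 41%.

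**Would confining the ICP analysis to completers bias it?** An illustration in SD units: normally distributed ICP, with the chance of loss rising with ICP through a logistic model (slope 1 or 2 per SD) and 20% loss in controls.
- No treatment effect, same loss mechanism in both arms: difference among completers about 0.
- True difference −0.5 SD: −0.45 SD (slope 1) or −0.40 SD (slope 2) among completers, an attenuation of 0.05 to 0.10 SD.

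This arises only under the restriction. Analysing everyone randomised avoids it.

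**The case against.** A reader might infer three stronger things, and the text does not support them.

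- *That the rule selects survivors.* The written trigger is technical. Death, recovery and planned catheter removal are not named. Early death enters only through the 3-day target, by an ambiguity and not by a stated intention.
- *That the rule contradicts intent-to-treat.* Patients are added and nobody is removed. Those with failed microdialysis are still treated as allocated, and an intent-to-treat analysis is planned. It can include the initial and the added patients alike.
- *That the worst ICP courses are screened out of the primary result.* Nothing in the article limits the ICP analysis to the 20 completers. Monitoring might also end early because a patient improves, which would select the other way. In the illustration above, even the restricted analysis is unbiased under no effect and only modestly attenuated otherwise.

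It can also be said that an uneven split does little harm: 12 × 8/20 = 4.8 against 10 × 10/20 = 5.0 keeps 96% of the efficiency, and a Mann–Whitney test remains valid. Letting microdialysis drive the size of an exploratory trial without a power calculation is a legitimate choice, and extra patients add ICP data. Investigators are blinded throughout, which largely covers the decision to add a patient. The additional files may define the analysis sets.

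All of this stands, and it narrows the point. It does not remove the conflict between the two uses of 20, or the mismatch between trigger and target, both of which lie in the article's own text.

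**Conclusion.** The stated sample size is contradicted within the protocol article: 20 enrolled (10 per arm) and 20 with at least 3 days of microdialysis data are the same number only if no patient falls short. At assumed shortfalls of 10%, 20% and 30%, about 22, 25 and 29 patients would be randomised on average, and an exact 10:10 split among the evaluable would occur in about 48%, 37% and 31% of trials. These figures rest on the assumed rates, equal loss in both arms and randomly ordered blocks of 4 and 6. The contradiction itself rests on none of them. The second defect is that a technical trigger is paired with a post-randomisation duration, so early death or withdrawal of monitoring with a working catheter may or may not lead to extra enrolment. The practical damage is limited: planned intent-to-treat remains feasible, and selection bias is conditional on an analysis that the article does not announce.

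**What to change.** 1. State that 20 is the number of patients with evaluable microdialysis, that the number randomised is 20 plus any additions, and give a maximum. Correct the 20 and 10/10 statements in the abstract, Trial population and eligibility, and Study participants.
2. Make target and trigger agree: add a patient only when microdialysis was not started for technical reasons or the catheter failed, judged blind to arm. A patient whose microdialysis ended through early death or withdrawal of monitoring counts as evaluable and prompts no addition.
3. State that every randomised patient, initial or added, is in the intent-to-treat ICP analysis, and that this analysis is the primary one. Use the set with at least 3 days of data only as support for the microdialysis outcomes.
4. Trial status estimated that recruitment would end on December 30, 2024. If it has closed, settle the wording before unblinding, and report the number randomised per arm with the reason for each addition.

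The cost is wording. The downside is that some patients in the microdialysis analysis will contribute fewer than 3 days of data.
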